**Other Information:**

147. Duration of normalization of respiratory rate. Hrs

148. Duration of disappearance of chest wall indrawing  Hrs

149. Duration of disappearance of dangers sign (s) (if any).  Hrs

150. Nosocomial infections 1=yes, 2=No

☐

#### SECTION 4: OUTCOME AND FOLLOW-UP

##### 151. Final Diagnosis:

1. Bacterial pneumonia

1=yes, 2=No

☐

2. PCJP

1=yes, 2=No

☐

3. PTB on the basis of MKJ scoring / WHO scoring

1=yes, 2=No

☐

4. PTB on the basis of AFB in gastric lavage

1=yes, 2=No

☐

5. PTB on the basis of positive gastric lavage culture

1=yes, 2=No

☐

6. Aetiology unknown

1=yes, 2=No

☐☐

##### 152. Final Outcome:

1. Well & discharged
2. Improved but still hypoxaemic on discharge
3. Did not improve but discharged on request
4. Died in hospital
5. Died at home
6. DORB
7. Absconded

☐

153. Did the patient develop "Treatment failure" from any arm?

☐

154. If death, cause of death:

1=Severe sepsis, 2=Septic shock, 3=Meningitis/encephalitis, 4=MODS, 5=Neonatal Sepsis, 6=severe electrolyte imbalance, 7= SAM, 9= not applicable

☐

155. Treatment on discharge:

1. Antibiotic course (e.g. amoxycillin, flucloxacillin, c'col etc)
2. TB treatment
3. Micronutrients

Physician's initials: \_\_\_\_\_

Date: \_\_\_\_/\_\_\_\_/\_\_\_\_

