## Research Design and Methods

Describe the research design and methods and procedures to be used in achieving the specific aims of the research project. If applicable, mention the type of personal protective equipment (PPE), use of aerosol confinement, and the need for the use BSL2 or BSL3 laboratory for different part of the intended research in the methods.. Define the study population with inclusion and exclusion criteria, the sampling design, list the important outcome and exposure variables, describe the data collection methods/tools, and include any follow-up plans if applicable. Justify the scientific validity of the methodological approach (biomedical, social, gender, or environmental).

Also, discuss the limitations and difficulties of the proposed procedures and sufficiently justify the use of them.

**Study design:** Open label, randomized, controlled intervention study in 308 children between two months to 59 months admitted to the Dhaka Hospital of icddr,b . Children will be randomized to receive (i) Amoxicillin plus single dose Gentamicin (ii) four doses of parenteral Ampicillin plus single dose Gentamicin. After 72 hours of treatment injectable Amoxicillin or injection Ampicillin will be switched to or replaced by oral Amoxicillin.

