### **Study Interventions:**

Children between 2 months to 59 months with severe pneumonia will be studied to evaluate the proportions of treatment failure in two different arms.

We will use sealed envelopes to randomly assign the children to either treatment arms. In first arm children will receive 2 daily doses of parenteral Amoxicillin and single daily dose of parenteral Gentamicin; and in 2nd arm, children will receive 4 daily doses of parenteral Ampicillin and single daily dose of parenteral Gentamicin. After 72 hours of treatment, injection Amoxicillin and injection Ampicillin will be replaced with oral Amoxicillin but injection gentamicin will be continued for total 5 days in once daily dose. During this time patient will be suggested to discharge from hospital and attend to Ambulatory care unit for getting once daily dose of injection Gentamicin. Both the treatment arm will continue for 5 days.

During the study period, children in both study arms will also receive standardized hospital management for diarrhoea and malnutrition (*Annex 2,3*).

“Treatment failure” will be standardized, based on clinical and monitoring data. Treatment failure is defined by the persistence of danger signs of severe pneumonia for >48 hours or deterioration within 24 hours of initiation of therapy or if child needs mechanical ventilation, dies at any time during hospital stay or left the hospital against medical advice.

During the study period any child from either study group who develops the features of “clinical failure” (any two of three criteria in the definition below) will be managed according to best practice in the clinical context. If children fail any arm of treatment, they should be rescued with second line antibiotic regimen, which is injection ceftriaxone and injection levofloxacin. Hypoxia will be managed by B-CPAP or humidified high flow air / O2 mix at 2 l/kg/min through nasal cannula.

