### **Sample size calculation:**

[For two-sample comparison of proportion (non-inferiority)]

Null hypothesis:  $p_2 - p_1 \leq \delta$  (inferior), where:  $p_i$  (entered in command) is the overall proportion of participants expect to experience the outcome if the treatments are non-inferior, and delta is the smallest change in proportions between groups ( $p_2 - p_1$ ) which would still be clinically important.

Assumptions:

power = 0.8; alpha = 0.025 (one-sided);  $p_i = 0.50$ ; delta = 0.16

Estimated required sample size (per group) = 154,

Total sample is 308

**Primary Outcome:** Treatment failure which is defined by the persistence of danger signs of severe pneumonia for >48 hours or deterioration within 24 hours of initiation of therapy (development of new danger signs or clinical signs of respiratory failure, or development of severe sepsis/meningitis, or, radiological deterioration).

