### **Intention to treat (ITT) analysis:**

It is essential to mention that the children who will be “absconded” from our study after randomization due to any reason will also be included in our primary analysis and will be considered them as INTENTION TO TREAT (ITT) ANALYSIS. Thus, ITT analysis should be, any child who, after randomization fulfil any following criteria:

1. Criteria for treatment failure as defined in the proposal
2. Receives intubation and / or mechanical ventilation
3. Dies during hospitalization
4. Left against medical advice

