## Data Safety Monitoring Plan (DSMP)

All clinical investigations (biomedical and behavioural intervention research protocols) should include the Data and Safety Monitoring Plan (DSMP) to provide the overall framework for the research protocol's data and safety monitoring. It is not necessary that the DSMP covers all possible aspects of each element. When designing an appropriate DSMP, the following should be kept in mind.

- a) All investigations require monitoring;
- b) The benefits of the investigation should outweigh the risks;
- c) The monitoring plan should commensurate with risk; and
- d) Monitoring should be with the size and complexity of the investigation.

Safety monitoring is defined as any process during clinical trials that involves the review of accumulated outcome data for groups of patients to determine if any treatment procedure practiced should be altered or not

Data safety Monitoring will be rigorously performed throughout the course of the study mainly by an independent DSMB who will visit randomly to review the forms for completeness, legibility, and internal consistency. icddr,b's ERC required reporting of all serious adverse events (SAE) within 24 hours; for this study all adverse events (AE) will also be reported by the study investigators to the DSMB within 24 hours of their occurrences using a standard case reporting form. As this is an open trial the implications of an adverse event can be better interpreted throughout the conduct of the trial than would be possible if any blinding was

involved. The DSMB will have full access to all case reporting forms and trial data, not only every 6 months, but whenever it is appropriate if there are any concerns over excess adverse events or unbalanced events between the three study groups. All aspects of intervention and interpretation will be performed according to rigorously standardized standards of procedures (SOPs).

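### The case record form holds treatment failure as one undated overall judgement by unblinded staff, and lacks the fields to derive or verify its most judgement-based parts

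*Protocol*

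**What the plan says.** The design is "Open label, randomized, controlled intervention study in 308 children between two months to 59 months". Under Study Interventions the protocol promises that failure "will be standardized, based on clinical and monitoring data". No rule linking those data to the endpoint is given, and no masked assessor or adjudication is described.

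The endpoint is defined in two ways:
- Project Summary and Study Interventions: danger signs lasting more than 48 hours, deterioration within 24 hours, need for mechanical ventilation, or a child who "dies at any time during hospital stay or left the hospital against medical advice".
- Specific Aims and Sample size calculation: persistence and deterioration only, with deterioration spelled out as "development of new danger signs or clinical signs of respiratory failure, or development of severe sepsis/meningitis, or, radiological deterioration".

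Study Interventions also refers to a clinical failure rule requiring two of three criteria in a definition said to follow. No such definition follows. The Intention to treat section points back to "Criteria for treatment failure as defined in the proposal" and lists ventilation, death and leaving against advice as separate entries.

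In the case record form (Annex 4), item 153 asks "Did the patient develop 'Treatment failure' from any arm". It lists no components and asks for no date of onset. The section closes with a physician's initials and one form date. The study group is entered on the same form at item 11. The budget justification gives one research physician both clinical assessment and prescribing.

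**The concern.** A single overall judgement made by someone who knows the arm is the kind of record in which expectation can move a borderline case. In a non-inferiority trial the direction matters. If borderline children on the new regimen are more readily called successes, the observed difference shrinks and a truly inferior regimen can pass. Leaning the other way costs power.

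Dated component data would let an analyst check item 153 or replace it. So the question is which components the form actually captures, and whether the gaps fall on the objective or the subjective ones.

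**Working it through.** **Step 1. Components against the form.**

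| Component | Field in Annex 4 | Derivable? |
|---|---|---|
| Death in hospital | Item 152 | Yes |
| Leaving hospital | Item 152: discharged on request, DORB, absconded | Yes, by proxy codes |
| Mechanical ventilation | Items 119, 127, 135 (days 1 to 3) | To day 3 only |
| Danger signs beyond 48 h | Item 149, "Duration of disappearance of dangers sign (s) (if any", in hours | Approximately; no time origin stated |
| Deterioration: respiratory failure | Respiratory signs on the day 1 page | In part |
| Deterioration: new danger sign within 24 h | Day 1 to 3 pages omit feeding, consciousness and convulsions; item 43 counts convulsions after admission without times | No |
| Deterioration: severe sepsis or meningitis | As an outcome, only among causes of death (item 154) | Not in survivors |
| Radiological deterioration | One undated chest X-ray field (item 140) | No |

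Item 141 adds dated antibiotics, including the two named for rescue. That is supporting evidence, not a component.

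The gaps fall mainly on deterioration, the part most dependent on judgement. It carries particular weight for some children. Entry needs two listed features, so a child can qualify through low oxygen saturation and severe distress with no danger sign. Persistence of danger signs then cannot apply, and deterioration is the main non-fatal route to failure.

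**Step 2. The plan's own figure.** Inputs from Sample size calculation: failure 0.50, margin 0.16, one-sided alpha 0.025, power 0.80.

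n per arm = 2 × 0.5 × 0.5 × (1.960 + 0.842)² / 0.16² = 153.3, rounded up to 154. This reproduces. Power at 154 per arm is 80.2%.

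**Step 3. Sensitivity to arm-dependent recording (illustration).** The protocol gives no misclassification rate, so every x below is an assumption. I also assume that non-inferiority is claimed when the upper 97.5% Wald limit of the risk difference lies below 0.16. With pA and pC the recorded failure proportions:

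SE = √[pA(1 − pA)/154 + pC(1 − pC)/154]

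P(claim) = Φ((0.16 − (pA − pC))/SE − 1.96)

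Take true failure at the margin, 58% on amoxicillin and 42% on ampicillin (mean 50%), with a fraction x of all amoxicillin failures unrecorded, so pA = 0.58(1 − x):

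- x = 0: difference 0.160; P = Φ(−1.96) = 2.5%.
- x = 5%: pA = 0.551, difference 0.131, SE = 0.0565; P = Φ(0.029/0.0565 − 1.96) = 7.4%. This is 0.05 × 0.58 × 154 ≈ 4.5 children.
- x = 10%: pA = 0.522, difference 0.102, SE = 0.0566; P = Φ(0.058/0.0566 − 1.96) = 17.5%. This is about 9 children.

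At 66% against 50% the same x gives 8.5% and 21.4%.

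If half of the failures were hard events recorded without error, x would act on the other half only. Then 5% behaves like 2.5% overall (pA = 0.5655, P = 4.4%) and 10% behaves like 5% (P = 7.4%).

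In the other direction, with true failure 50% in both arms and amoxicillin over-recorded by 2 or 5 percentage points, power falls from 80% to 69% or 49%.

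For scale: with 77 of 154 control failures, 84 amoxicillin failures pass (upper limit 15.7%) and 85 do not (16.3%).

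**The case against.** The strongest reply is that much of the composite is recorded elsewhere on the form, so a reader who infers that it cannot be split at all is wrong. Step 1 confirms this: death, departures, early ventilation and, roughly, danger-sign persistence are separable. A result carried by soft elements could be compared with the hard ones.

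A reader might also infer that the physician's opinion is the primary analysis variable. The protocol does not say so. It promises a standardised, criteria-based endpoint, and a statistical analysis plan that is not shown may define the derivation. That stands, but no plan can derive what the form never collects.

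The error rates above are assumed, run in one direction, and in their full form let misclassification reach deaths and ventilation, which are hardly open to opinion. This stands too. They show sensitivity and are not estimates.

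Splitting one box into several leaves the same unblinded staff filling them in. That is correct: the gain lies in verifiability and in less room for overall opinion.

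Two pieces of apparent evidence carry no weight here. The absence of a yes/no key at item 153 may be an effect of text extraction. The monitoring plan's remark, "As this is an open trial the implications of an adverse event can be better interpreted", concerns adverse events and not endpoint assessment.

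**Conclusion.** The point holds in a limited form, and the change is worth making. Item 153 is a single undated overall judgement made without masking. The form lacks the fields to derive or check new danger signs within 24 hours, severe sepsis or meningitis in survivors, radiological deterioration and ventilation after day 3. The 48-hour rule rests on a duration with no stated starting point.

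Neither the direction nor the size of any bias can be known from the protocol. Under the assumptions shown, a false claim rises from 2.5% to about 7% or 17% when 5% or 10% of all amoxicillin failures go unrecorded, and to about 4% or 7% if only half of failures are open to judgement. The sample size of 154 per arm is unaffected.

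**What to change.** 1. Reconcile the two definitions of treatment failure (Project Summary and Study Interventions against Specific Aims and Sample size calculation), and resolve the two-of-three criteria for clinical failure, which are invoked but not defined. The form cannot be corrected until this is settled.
2. Add the three danger signs to the day 1, 2 and 3 pages.
3. For each component of the reconciled definition, add a yes/no field with date and time, counted from the first study dose. Give item 149 the same time origin.
4. State in the Data analysis plan that failure is derived from these fields by a fixed rule and not taken from item 153, and that each component is tabulated by arm.

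The cost is about half a page of the form and a short derivation program. It needs no new assessor and no change in sample size. It limits ascertainment bias without eliminating it, because the bedside observer still knows the arm.

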## Annex 5 Gender Analysis Framework:

Efficacy of two doses of parenteral Amoxicillin plus single dose Gentamicin compared to four doses of parenteral Ampicillin plus single dose Gentamicin in managing children under five with severe pneumonia: an open labelled randomized controlled clinical trial

| In Relation to Severe pneumonia                                                                                  | Are there sex differences in                                                                                                                                                                                   | How do biological differences between women and men influence their :                        | How do the different roles and activities of men and women affect their:                                                                                                | How do gender norms / values affect men and women’s      | How do access to, and control over resources affect men and women’s                                                        |
|------------------------------------------------------------------------------------------------------------------|----------------------------------------------------------------------------------------------------------------------------------------------------------------------------------------------------------------|----------------------------------------------------------------------------------------------|-------------------------------------------------------------------------------------------------------------------------------------------------------------------------|----------------------------------------------------------|----------------------------------------------------------------------------------------------------------------------------|
| Vulnerability:
Incidence
**
Prevalence
**
(male/female) | No sex difference found in any published literature. However after completion of this study we will have a overview of the prevalence of severe pneumonia                                               | Not applicable because biological differences do not make someone more hypernatremic. | No role yet found                                                                                                                                                | Not applicable                                    | As it is a hospital based study access and control over resources will be according to the hospital existing Policy |
| Health seeking behaviour                                                                                  | No studies yet found any difference in this context                                                                                                                                                     | Not applicable                                                                        | Although there is common practise in society to give less attention to female children, but in this hospital based controlled setting this issue will be averted | No gender norms in Same as above Severe pneumonia |                                                                                                                            |
| Ability to access health services                                                                         | Access to health services is among different sex group has been minimized                                                                                                                                      |                                                                                              |                                                                                                                                                                         |                                                          |                                                                                                                            |
| Experience with health services and health providers                                                      | No published literature has shown any difference i this issue however according to current hospital practise in icddr,b all patient will receive equal health service and there will be no gender norms |                                                                                              |                                                                                                                                                                         |                                                          |                                                                                                                            |
| Preventive and Treatment options, responses to treatment or rehabilitation                                | Not related to this study                                                                                                                                                                               |                                                                                              |                                                                                                                                                                         |                                                          |                                                                                                                            |

| In Relation to Severe pneumonia                             | Are there sex differences in          | How do biological differences between women and men influence their : | How do the different roles and activities of men and women affect their:                                                                                | How do gender norms / values affect men and women's | How do access to, and control over resources affect men and women's |
|--------------------------------------------------------------------|----------------------------------------------|------------------------------------------------------------------------------|----------------------------------------------------------------------------------------------------------------------------------------------------------------|------------------------------------------------------------|----------------------------------------------------------------------------|
| Outcome of health problem                                   | There is evident in different sex in outcome | Not applicable                                                        | No published literature has shown any difference in outcome , gender norms will not be affected in this hospital setting of severe pneumonia management |                                                            |                                                                            |
| Consequences (economic & social, including attitudinal) | Not related                           | Not known                                                             | Not yet been addressed                                                                                                                                  |                                                            |                                                                            |

[figure not shown]
